## Abstract

**Background:**

Cardiovascular diseases (CVD) are the leading cause of death and the third cause of disability in Europe. Prevention programmes should include interventions aimed at a reduction of medical risk factors (hypertension, hypercholesterol, hyperglycemia, overweight and obesity) as well as behavioural risk factors (sedentary lifestyle, high fat intake and low fruit and vegetable intake, smoking). The aim of this study is to investigate the effects of a multifaceted, multidisciplinary electronic prevention programme on cardiovascular risk factors.

**Methods/Design:**

In a randomized controlled trial, one group will receive a maximal intervention (= intervention group). The intervention group will be compared to the control group receiving a minimal intervention. An inclusion of 350 patients in total, with a follow-up of 3 years is foreseen. The inclusion criteria are age between 25–65 and insured by the Onderlinge Ziekenkas, insuring for guaranteed income in case of illness for self-employed. The maximal intervention group receives several prevention consultations by their general practitioner (GP) using a new type of cardiovascular risk calculator with personalised feedback on behavioural risk factors. These patients receive a follow-up with intensive support of health behaviour change via different methods, i.e. a tailored website and personal advice of a multidisciplinary team (psychologist, physiotherapist and dietician). The aim of this strategy is to reduce cardiovascular risk factors according to the guidelines. The primary outcome measures will be cardiovascular risk factors. The secondary outcome measures are cardiovascular events, quality of life, costs and incremental cost effectiveness ratios. The control group receives prevention consultations using a new type of cardiovascular risk calculator and general feedback.

**Discussion:**

This trial incorporates interventions by GPs and other health professionals aiming at a reduction of medical and behavioural cardiovascular risk factors. An assessment of clinical, psychological and economical outcome measures will be performed.

**Trial registration:**

ISRCTN23940498

## Background

In Europe, cardiovascular disease (CVD) is the leading cause of death (1.5 million deaths per year) and is an important source of disability [1-3]. The incidence of coronary vascular events is 1.91 per 1000 population years [4]. It is proven that prevention of CVD risk factors lead to a reduction of CVD[5,6]. Prevention programmes should include interventions aimed at a reduction of medical risk factors (hypertension, hypercholesterolaemia, hyperglycaemia and overweight) and behavioural risk factors (sedentary lifestyle, high fat intake and low fruit and vegetable intake, smoking) for CVD[7,8] The individual contributions of these risk factors to CVD are: high blood pressure (62%), high cholesterol (18%), overweight (13%), low fruit and vegetable intake (11%), physical inactivity (7%), tobacco (12%) and alcohol (4%). The joint contribution of these risk factors is 70–76%[9]. Recent guidelines advise to determine the overall risk on CVD using the SCORE Model, scoring the individual risk in terms of the absolute 10 year probability of developing a fatal cardiovascular event[3]. Furthermore, treatment should be targeted to all medical and behavioural risk factors i.e. stimulating physical activity, aiding healthy food choices and encouraging non-smoking[3,10]. Online health advice instruments can be used as a tool to aid behavioural change[11]. The implementation of prevention programmes has to be cost effective. Reduction of cardiovascular risk factors seems to be cost effective [12-14]. To conclude, it is important to implement cost effective CVD prevention programmes to decrease CVD (risk factors) and associated costs[3]. The aim of the PreCardio-study is to determine the effects of a computer-tailored cardiovascular prevention programme with the general practitioner (GP) as a key figure. This prevention programme consists of interventions targeted at all risk factors with the use of information and communication technology (ICT) at different levels. At GP-level, a tool for computer-assisted cardiovascular risk screening and an informational website will be implemented. At patient-level, a personalised website with tailored advice will be foreseen.

## Methods/Design

### Study population

PreCardio is a randomized controlled trial. Approval was obtained from the ethics committee of the University Hasselt. A total of 350 subjects will be included in the study with a follow-up of 3 years. The inclusion criteria are age between 25–65 and insured by the Onderlinge Ziekenkas, insuring for guaranteed income in case of illness for self-employed. All study participants need to sign an informed consent and have access to the internet. Other eligitability criteria are not included.

### Recruitment

The **study participants **will be recruited through various channels. Firstly, all potential participants are insured by "De Onderlinge Ziekenkas". This membership gives the study secretariat access to necessary contact information. Secondly, all of the insured are self-employed, most of them lawyers. This provides the study office with two advantages: (1) communication is possible at the worksite and (2) the prevention programme is even more tailored to the uniform target group. The announcement of the study was already made through mass-media announcement (e.g. national newspapers, provincial journal and radio) but will be intensified at the worksites of the potential participants. Together with the involved Bars (of the province of Limburg in the East of Belgium) mass mailings and promotional activities at the worksite (e.g. information, fruit distribution,) will be organized. Thirdly, a large event will be organised for the participants of the intervention group and control group. Before joining these events a written informed consent, downloadable on a website with brief information, should be signed and mailed back to the study secretariat. At this large event general information about PreCardio will be given, a first screening and the ability to purchase health-related products.

The **general practitioners (GP) **that will participate in the study are GPs of the province of Limburg, situated in the East of Belgium. They will be recruited with involvement of their own provincial general GP platform "Limburgs Huisartsenplatform" and provincial institutions involved in health "LOGOs". Together with the GP platform and the LOGOs mass mailings to GPs of Limburg will be organised. Moreover, minimal two information sessions for GPs will be organised in the university building with information about the study and education about a new type of cardiovascular risk calculator will be offered. All participating GPs need to sign an informed consent and have access to the internet for downloading an electronic cardiovascular risk screenings programme based on the European Guidelines for CVprevention[3].

### Randomization

The study participants were randomized using a nonstratified randomization technique with a known probability. Each participant had a 67% chance to be allocated to the intervention group. The randomization was performed by an independent person. The names of the participants were written on papers that were put in sealed envelopes. Next, the envelopes were randomly assigned by hand to two baskets for the intervention and the control group, respectively, with a ratio of 2/1.

### Overall aim of the study

To examine the effects of medical and behavioural interventions on medical cardiovascular risk factors such as hypertension, hypercholesterolaemia and hyperglycaemia and behavioural risk factors such as a sedentary lifestyle, an unhealthy diet and smoking. Furthermore, the impact of changes in medical and behavioural risk factors on overall cardiovascular risk will be investigated.

#### Primary aims

1. To examine the effects of medical and behavioural interventions on medical parameters such as systolic blood pressure, diastolic blood pressure, total blood cholesterol level, blood glucose level (HbA1c), overweight and obesity, BMI.

2. To examine the effects of medical and behavioural interventions on health related behaviour such as physical activity; fat; fruit and vegetable intake; and smoking behaviour.

3. To examine the effects of medical and behavioural interventions on overall cardiovascular risk mediated by changes in medical and/or behavioural risk factors.

4. To determine the proportion study participants with a 10% reduction in systolic blood pressure with participants with hypertension

5. To determine the proportion study participants with a 10% reduction in diastolic blood pressure with participants with hypertension

6. To determine the proportion study participants with a 10% reduction in total cholesterol with patients with hypercholesterol

7. To determine the proportion study participants with a 10% reduction in HB1Ac with initial HB1Ac >7% (high risk)?

8. To determine the proportion study participants with a 10% reduction in weight with initial BMI >25 kg/m^2^?

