### Analysis and power

A power calculation was performed to determine the number of study participants needed to detect a significant effect of the PreCardio prevention programme. A t-test will be used to compare the means of the outcome measures from the intervention and the control group. The sample size calculation is based on the population standard deviation of the primary outcome measure. For PreCardio, this is, for instance, systolic blood pressure. Kelley *et al *found a mean systolic blood pressure of 125 mm/Hg (SD 14 mm/Hg)[42]. The sample size calculation was performed with Nquery Advisor 4.0^®^. A two group t-test with a 0,05 two-sided significance level will have 82% power to detect the difference between a Group 1 mean of 120 mm/Hg and a Group 2 mean of 125 mm/Hg, a difference in means of -5 mm/Hg, assuming that the common standard deviation is 14 mm/Hg, when the sample sizes in the two groups are 200 and 100, respectively (a total sample size of 300). Other outcome measures were also used to determine the necessary sample size. A recent study about the effect of a computer-tailored intervention to reduce fat intake included at post-test a mean fat intake of 85 grams/day (SD 34.5 grams/day) [43]. A two group t-test with a 0,050 two-sided significance level will have 80% power to detect the difference between a Group 1 mean of 85 grams/day and a Group 2 mean of 97 grams/day, a difference in means of -12 grams/day assuming that the common standard deviation is 34.5 grams/day, when the sample sizes in the two groups are 200 and 100, respectively (a total sample size of 300). Another study evaluating a website-delivered computer-tailored intervention for increasing physical activity increased physical activity with a mean of 77 minutes in the intervention group [44]. In this study the total moderate- and vigorous-intensity physical activity was chosen as an outcome measure. This measure can be used to determine the necessary sample size to detect a difference in means in the present study. At follow up this measure had a mean of 363 minutes (SD 323) for the intervention group and 241 minutes (SD 269) for the control group [43]. A two group t-test with a 0,05 two-sided significance level will have 86% power to detect the difference between a Group 1 mean of 363 minutes and a Group 2 mean of 241 minutes, a difference in means of 122 minutes, assuming that the common standard deviation is 323 minutes, when the sample sizes in the two groups are 200 and 100, respectively (a total sample size of 300).

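### Primary aims 4 to 8 are 10% responder proportions in high-risk subgroups, worded without a control contrast, while the sample size supports only whole-sample comparisons of means

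*Protocol article*

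**What the plan says.** The Primary aims section of the protocol article lists eight aims of equal rank. Aim 1 is an effect question on continuous variables: "To examine the effects of medical and behavioural interventions on medical parameters such as systolic blood pressure, diastolic blood pressure", followed by total cholesterol, HbA1c, overweight and BMI. Aims 4 to 8 are of another kind. Aim 4 reads "To determine the proportion study participants with a 10% reduction in systolic blood pressure with participants with hypertension". Aims 5 and 6 repeat the form for diastolic pressure and total cholesterol. Aim 7 reads "To determine the proportion study participants with a 10% reduction in HB1Ac with initial HB1Ac >7% (high risk" and aim 8 "To determine the proportion study participants with a 10% reduction in weight with initial BMI >25 kg/m^2". None of these five mentions the arms.

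A comparison is stated elsewhere. The abstract says "The intervention group will be compared to the control group receiving a minimal intervention", and Analysis and power says "A t-test will be used to compare the means of the outcome measures from the intervention and the control group". That section also names a linear regression, but only for change in overall cardiovascular risk. For systolic pressure, "A two group t-test with a 0,05 two-sided significance level will have 82% power" to detect 120 against 125 mmHg, "assuming that the common standard deviation is 14 mm/Hg, when the sample sizes in the two groups are 200 and 100". The other two calculations, for fat intake and physical activity, also concern means at 200 and 100. None covers a subgroup or a proportion.

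The Study population section plans 350 participants and does not require a raised risk factor for entry. Randomization is 2:1 without stratification.

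**The concern.** Two things are fixed badly.

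First, the aims as worded can be met by quoting one percentage. If people are selected because their first value is high, their mean falls on re-measurement even when nothing has changed, and some of them cross a 10% threshold. Both arms also receive a GP consultation at which treatment can be started, so falls are to be expected in the control arm too. A responder percentage shown without its control counterpart therefore says little about the programme.

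Second, primary status implies that the trial can answer the question. Entry is unselected, so each subgroup is only part of the sample, and cutting a continuous change at 10% loses further information. A negative result on such an aim could easily occur with a programme that achieves the effect it was planned for, and it would stand in the report as a negative primary result.

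**Working it through.** **Inputs from the protocol article.** SBP mean 125, SD 14, effect 5 mmHg, two-sided 0.05, arms of 200 and 100 (Analysis and power); 350 planned (Study population); ratio 2:1 (Randomization).

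**Assumptions not in the document.** Hypertension means baseline SBP of 140 or more; baseline and follow-up are bivariate normal with equal SD; correlation r runs from 0.5 to 0.9; there is no true change in the control arm and a uniform 5 mmHg shift in the intervention arm. All rates and prevalences for HbA1c and weight are also assumed.

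**1. The plan's own figure.** SE = 14 × √(1/200 + 1/100) = 1.715. Power ≈ Φ(5/1.715 − 1.96) = Φ(0.956) = 83.1%; the exact t calculation gives 82.8%. The stated 82% is reproduced.

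**2. Size of the SBP subgroup.** P(SBP ≥ 140) = 1 − Φ(15/14) = 14.2%. That is 0.142 × 300 ≈ 43 people, or 0.142 × 350 ≈ 50 (33 against 17).

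**3. Regression to the mean.** The mean baseline in this subgroup is 125 + 14 × φ(1.071)/0.142 = 147.2, which is 22.2 above the overall mean. The expected fall with no effect is (1 − r) × 22.2: 11.1 mmHg at r = 0.5, 6.6 at 0.7 and 2.2 at 0.9. A 10% fall from 147 is about 15 mmHg, so a share of the subgroup crosses it by chance.

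**4. Responder rates and power.** A responder has follow-up ≤ 0.9 × baseline. Rates come from simulating the bivariate normal, and numerical integration agrees. Power is for a two-sided comparison of two proportions, 2:1.

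| r | Responders, no effect | Responders, 5 mmHg effect | Power, N = 300 | Power, N = 350 |
|---|---|---|---|---|
| 0.5 | 38% | 54% | 16% | 18% |
| 0.6 | 30% | 47% | 17% | 19% |
| 0.7 | 21% | 38% | 18% | 21% |
| 0.8 | 11% | 27% | 18% | 21% |
| 0.9 | 2% | 11% | 11% | 13% |

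One cell in full (r = 0.6, N = 350): p = 0.303 and 0.470, n = 16.6 and 33.1, pooled p = 0.414. The SE under the null is 0.148 and under the alternative 0.142. Power = Φ((0.167 − 1.96 × 0.148)/0.142) = Φ(−0.87) ≈ 19%. Fisher's exact test in simulated trials of 200/100 gave 11 to 14% for r between 0.5 and 0.7.

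**5. Sensitivity.** If 30 to 50% of 350 were hypertensive with the same responder rates, power would be 32 to 67%. A 10 mmHg effect in about 50 hypertensive participants gives 57 to 79%.

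**6. HbA1c and weight.** If 1 to 5% have HbA1c above 7% (4 to 18 of 350), power for 20% against 50% is 6 to 20%. For weight (assumed mean 80, SD 14 kg, selection above 80 kg), regression to the mean alone gives about 0.6 to 5% responders at correlations of 0.97 to 0.93. With 40 to 60% above BMI 25, power is 15 to 21% for 5% against 10%, and 68 to 87% for 5% against 20%.

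**7. The alternative for SBP.** Adjusting for baseline reduces the SD to 14 × √(1 − r²): 12.1 at r = 0.5 and 10.0 at r = 0.7. With 200 and 100, the SE is 1.485 and 1.224. Power is Φ(5/1.485 − 1.96) = 92% and Φ(5/1.224 − 1.96) = 98%.

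**The case against.** The strongest reply is that this is a randomized trial with a stated between-arm comparison. Regression to the mean acts on both arms alike, so a contrast of responder proportions would be unbiased, and nothing in the article says that the proportions will be reported for one arm only. That stands. A reader might infer from aims 4 to 8 that no control comparison is planned, or that the trial result is biased by selection on high values; the abstract and Analysis and power support neither.

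It can also be said that a test for binary outcomes belongs to the analysis plan. That stands too, and the lack of a named test is not the point here. What the article does fix is the rank of these aims, their wording and the basis of the sample size.

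A reader might go further and say that all five aims yield many false responders and have almost no power. The figures do not carry that. Only SBP can be modelled from the plan's own inputs, and even there the cut-off and the correlation are assumed. Hypertension is not defined in the text shown; only aims 7 and 8 refer to an initial value, and treated people with normal readings may count under aims 4 and 5, which would weaken the regression. The share above 140 comes from a cited study, not from this cohort. For weight, the chance response is small and power can exceed 80%.

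Finally, aim 1 already asks the continuous question, so rewriting aims 4 to 8 as continuous comparisons would largely duplicate it. This is correct, and the fix below leaves them as proportions and changes their rank and reporting.

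**Conclusion.** The point holds in a limited form. Aims 4 to 8 have primary status, name no contrast, and fall outside what the sample size was computed for. The planned randomized comparison remains valid; the misreading arises only if a proportion is interpreted without the control arm. For SBP that could mean crediting about 21 to 38% response to no effect at correlations of 0.7 to 0.5, falling to 2% at 0.9.

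At the plan's own SBP figures and an assumed cut-off of 140, the between-arm responder comparison has about 11 to 21% power. This is low but specific to those inputs: a larger hypertensive share or a larger effect raises it considerably. For HbA1c above 7%, power is likely very low, because few unselected adults would qualify (assumed 1 to 5%). For weight no general statement is possible. No figures were computed for diastolic pressure or cholesterol.

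**What to change.** Make the continuous outcomes of aim 1 (systolic and diastolic pressure, total cholesterol, HbA1c, BMI or weight) the primary analysis. Compare the arms in the full sample by ANCOVA adjusted for the baseline value, in place of the unadjusted t-test. Table 1 already schedules these measurements at month 0; the Design section puts HbA1c in brackets, so it should be confirmed that it is taken in everyone. Add an arm-by-baseline term as a supporting analysis, to show whether the effect differs at high starting values.

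Move aims 4 to 8 to secondary or descriptive status. Define each subgroup by baseline values, including what counts as hypertension and raised cholesterol. Report the responder proportions for both arms, with the risk difference and its confidence interval, and never as a single percentage.

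The cost is wording only: no new data and no more participants. The small downside is that the responder percentages lose primary status.

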#### Secondary aims

1. To determine the incidence of cardiovascular events

2. Number and total costs of cardiovascular events leading to loss of productivity

3. To examine the effects of medical and behavioural interventions on psychological constructs as stage of change, attitude towards behaviour, self-identity, perceived behavioural control, autonomous motivation, intention.

4. To examine the effects of medical and behavioural interventions on Health Related Quality of Life.

5. To examine the effects of social support on health related behaviour (physical activity, fat and fibre intake and smoking behaviour) and psychological constructs (stage of change, attitude towards behaviour, self-identity, perceived behavioural control, autonomous motivation, intention)

6. To perform a cost-effectiveness analysis of the medical and behavioural interventions using incremental cost-effectiveness ratios

### Design

The intervention group as well as the control group receive a first medical prevention consultation with a GP of their choice. Fig 1 represents the study design. The GP performs a cardiovascular risk assessment using an adapted risk assessment flowchart (Fig 2). Medical data such as systolic and diastolic blood pressure, total blood cholesterol, LDL cholesterol (and HbA1c) are collected at this medical prevention consultation prior to risk determination. The intervention and the control group receive the therapeutic goals from the risk assessment flowchart. The intervention group receives supplementary tailored feedback regarding behaviour change based on the TransTheoretical Model or the Stages of Change Model[23]. Thus, the feedback is tailored to the stage of change the study participants are in for physical activity, diet and quit smoking. After the first medical prevention consultation all study participants get access to a website which includes a question list for baseline data collection. The intervention group receives tailored advice on this question list. The control group receives general advice to impede or avoid drop-out but with caution for causing bias. The question list includes items for physical activity assessment, fat intake assessment, fruit and vegetable intake assessment, smoking behaviour assessment and assessment of psychological variables. The physical fitness will be determined at the GP's office, at study participants home and at baseline data collection during the large event. For follow-up data collection these assessments will take place regularly. The intervention group receives the maximal intervention and the control group receives the minimal intervention.

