### Interventions

#### Minimal intervention

##### Medical prevention consultation

The interventions targeted on medical parameters include a first medical prevention consultation with the GP. In this medical prevention consultation the cardiovascular risk (risk on having a heart attack in the next 10 years) will be calculated using a new computer programme. This computer programme is called "Electronic Prevention Record" (EPR). Innovative about the EPR is its connection to "Electronic Medical Record" (EMR). The EMR is also a computer programme, a record about the medical history and treatment provided to the patient. In the province of Limburg, the setting for the PreCardio-study, 75% of the GPs use an EMR[36]. In Belgium, 70% of the GPs use an EMR [37]. In Belgium there are 17 different providers of EMRs. The EPR generates, after a limited input (thanks to the connection to the EMR), the cardiovascular risk, the therapeutic goals (targeted on medical parameters and behaviour change) and a target date for the next follow-up consultation. This date is dependent on the determined cardiovascular risk. During these medical prevention consultations medical practice will be performed: measurement (e.g. blood pressure) and installation of treatment to influence medical parameters. Supplementary, the GP performs stage of change assessment (Table 2) using the EPR. The GP asks for PA and diet which statement fits the participant's situation best. If it is a smoker, the stage of change for quitting smoking is assessed as well. The stage of change assessment is for the control group not followed by tailored feedback for behaviour change.

All data collected at the medical prevention consultation are stored in the EPR that is connected to the EMR (Fig 4). Therapeutic goals in line with cardiovascular risk are determined. These goals, together with the data provided by the study participant are electronically sent to the study office by a secured connection. The information from the intervention group is closely examined and the participants of the intervention group will receive a reminder from the study office when it is time to plan their next medical prevention consultation.

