#### Maximal intervention

##### Medical prevention consultation + tailored feedback + reminder from study office

The maximal intervention includes the medical prevention consultation described under the minimal intervention. However, the maximal intervention includes two extra services in relation to the medical prevention consultation.

Firstly, supplementary to the therapeutic goals which are communicated to the patient, the intervention group receives tailored feedback according to the stage of change the study participant is in. For this purpose, the table to for stage of change assessment (Table 2) is included in the EPR. The GP asks for PA and diet which statement fits the participant's situation best. If it is a smoker, the stage of change for quitting smoking is assessed as well. Following this stage determination, the GP gets information about the stage of change the study participant is in for each behaviour, namely: precontemplation, contemplation, preparation, action or consolidation[23]. The tailored feedback that follows is also based on principles from Motivational Interviewing (MI) [39]. Tailored feedback following a classification in the contemplation stage for smoking gives the GP following information: "Accept and talk about the ambivalence of the patient regarding quitting to smoke"; "Talk with the patient about the advantages and disadvantages of smoking and quitting smoking. Don't give arguments to quit smoking yourself"; "Advise the patient to download the quitting to smoke leaflet on the personalised website"; "Advise the patient to look at step 1 and step 2 of the quitting to stop manual on the personalised website". Tailored feedback can be easily printed and given along with the participant by the GP. This printed tailored feedback for the participant following a classification in the contemplation stage for smoking contains following information: "You want to quit smoking and you know it could have advantages, but something keeps you from actually quitting"; "It can be a good idea to think about the advantages and disadvantages of smoking and quitting to smoke. The quitting to smoke manual (step 1 and step 2) on the website can be an aid in this process"; "You can also download a quitting to smoke leaflet". This kind of advice is given to every study participant in the intervention group for all relevant health behaviours.

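### Follow-up blood pressure is read by a GP who knows the arm, so differential reading bias raises the false-positive risk for the blood-pressure aims

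*Protocol article*

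**What the plan says.** **Who measures.** The Design section of the protocol article says: "The GP performs a cardiovascular risk assessment using an adapted risk assessment flowchart (Fig 2". Blood pressure is collected in that consultation, before the risk is determined. Table 1 names the GP as the means of obtaining BMI, blood pressure, cholesterol and HbA1c at 0, 12, 24 and 36 months, with risk-dependent visits at 4 and 8 months. The minimal-intervention section places measurement and the start of treatment in the same consultation.

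**Who delivers the arm-specific part.** In the maximal intervention, the GP's electronic prevention record (EPR) shows the GP guidance matched to the participant's stage of change, and "Tailored feedback can be easily printed and given along with the participant by the GP". For controls, "The stage of change assessment is for the control group not followed by tailored feedback for behaviour change".

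**Where blood pressure is used.** Systolic and diastolic pressure are named in primary aim 1. Their 10% reductions in participants with hypertension are primary aims 4 and 5. Overall cardiovascular risk is primary aim 3 and the outcome of the planned linear regression; Table 1 lists blood pressure among the components of that risk assessment.

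**Sample size.** Analysis and power takes systolic pressure first ("For PreCardio, this is, for instance, systolic blood pressure") and then adds: "Other outcome measures were also used to determine the necessary sample size". Those others are fat intake and physical activity.

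**The concern.** One professional both gives the component that distinguishes the arms and takes a reading that serves as an outcome. A blood pressure taken by hand leaves room for rounding, for repeating an unwelcome value and for choosing which value to record. If these habits differ by arm, even slightly, the difference adds directly to the treatment contrast. It does not shrink as the sample grows, and the planned t-test and regression cannot remove it.

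The article considers contamination of the control group and is careful about the advice given to controls, but it does not discuss this route. At stake is the reading of a significant blood-pressure difference, and of the responder proportions and risk score derived from the same values.

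**Working it through.** **Inputs**, all from Analysis and power:
- test and planned power: "0,05 two-sided significance level will have 82% power";
- effect and spread: "a difference in means of -5 mm/Hg, assuming that the common standard deviation is 14 mm/Hg";
- group sizes: "when the sample sizes in the two groups are 200 and 100, respectively (a total sample size of 300".

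Randomization gives the 2:1 ratio, and Study population gives the enrolment target of 350. The size of any reading bias is not in the documents; the values used below are assumptions.

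**Step 1: reproduce the stated power.** SE = SD × √(1/n₁ + 1/n₂) = 14 × √(1/200 + 1/100) = 14 × √0.015 = 1.715 mmHg. With 298 degrees of freedom the critical t is 1.968. The noncentrality is 5/1.715 = 2.92, and the noncentral t distribution gives power of 82.8% (normal approximation 83.0%). This agrees with the stated 82%.

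**Step 2: smallest significant difference.** 1.968 × 1.715 = 3.37 mmHg.

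**Step 3: pure bias.** Set the true effect to zero and let readings differ systematically between arms by b mmHg in favour of the intervention. The probability of a significant result in that direction is 1 − F(t_crit; df, b/SE), where F is the noncentral t distribution function. With b = 0 it is 2.5%.

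| Assumed bias b (mmHg) | Share of the 5 mmHg target | 200/100 | 233/117 (all 350 analysed) |
|---|---|---|---|
| 0 | 0% | 2.5% | 2.5% |
| 1 | 20% | 8.4% | 9.2% |
| 2 | 40% | 21.3% | 24.1% |
| 3 | 60% | 41.4% | 47.0% |
| 3.4 | 68% | 50.7% | 57.0% |

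The last column uses SE = 14 × √(1/233 + 1/117) = 1.586 mmHg and a threshold of 3.12 mmHg. The larger sample makes a fixed bias more likely to reach significance, because the SE falls and the bias does not.

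**Step 4: which readings are exposed.** At the first visit, data collection precedes risk determination, and the tailored feedback follows the stage assessment. Nothing shows that the GP knows the arm before the baseline reading. By 12, 24 and 36 months, the GP has already given tailored feedback or seen that none followed. The exposed readings are therefore the follow-up values, which carry the treatment effect.

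**The case against.** Several points on the other side are fair.

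- **A condensed article.** Device and reading procedure may stand in a full protocol that is not shown. Their absence alone would be no finding. What stands is what the article states: it gives both roles to the GP, and a device instruction would not change the GP's knowledge of the arm.
- **Sizing and success.** A reader might infer that blood pressure is the outcome on which the trial was sized and that a modest bias makes the trial positive. The documents do not support this. Systolic pressure is one of three sizing outcomes, and the other two come from website questionnaires. There are eight primary aims and no single success rule, so the figures concern a significant blood-pressure result only. Even then, a bias of 2 mmHg leaves about 79% of null trials, and 3 mmHg about 59%, without a significant benefit.
- **Baseline.** A reader might also infer that baseline values are compromised. The order of events in the article does not show that.
- **Direction.** GPs set goals and start treatment in both arms, and reminders, website and team support come from others. A bias towards the intervention is plausible, not demonstrated.
- **Continuity.** The article says only that the first consultation is with a GP of the participant's choice. That the same GP takes every later reading is inferred.

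Unblinded measurement is common in pragmatic primary-care trials. That bears on how serious the point is, not on whether it exists.

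**Conclusion.** The point holds as a limited design weakness. The GP's knowledge of the arm at follow-up comes from the design as described, and blood pressure feeds four of the eight primary aims. If readings differed by 1 to 3 mmHg in favour of the intervention with no true effect, a significant benefit on systolic pressure would appear in about 8% to 41% of trials at 200/100, or about 9% to 47% with all 350 analysed, against 2.5%. An even chance needs about 3.4 mmHg at 200/100, roughly two thirds of the target difference.

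These figures rest on the article's SD of 14 mmHg, a t-test of means, and a bias whose size and direction are assumed. They show how sensitive the result is; they do not predict that such bias will occur. The point does not extend to the questionnaire outcomes, and cholesterol and HbA1c are less exposed to the reader. It justifies a cheap improvement in measurement, not a change of design.

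**What to change.** 1. In both arms and at every visit, define the outcome blood pressure as the mean of at least two consecutive readings from an automated device, entered in the EPR exactly as displayed and not editable afterwards. This is the part that protects the follow-up values.
2. At the first visit, have the EPR take these values before it shows the arm or any tailored feedback. This is a minor addition that secures the baseline.
3. State as a limitation that follow-up readings are taken by a GP who is not blinded.

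Two other measures look attractive but would not do the job. Requiring entry before the stage-of-change screen opens cannot mask a GP who already knows the arm from an earlier visit. Cholesterol and HbA1c cannot serve as a check on a blood-pressure effect, because a real effect on pressure need not appear in them.

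The cost is that GPs must use an automated device, the EPR needs a small change, and each visit takes slightly longer. The instruction can be given at the GP information sessions already planned. No extra participants, visits or staff are needed.
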